#### Safety

The safety analysis includes the calculation of frequencies and incidence rates as well as incidence rate ratios and corresponding 95% confidence intervals of adverse and serious adverse events using Poisson regression or negative binomial regression models depending on the distribution of the variables.

Secondary endpoints: All secondary outcomes will be analyzed using appropriate statistical regression models and by accounting for the particular baseline values (analysis of covariance), center, rnTMS training duration, and age. In the case of measuring endpoints at several time points, we will use mixed regression models to account for the dependencies of the data. A detailed statistical analysis plan will be written and published before the database is closed.

### Interim analyses {21b}

No interim analyses are planned in this study. (S)AEs will be carefully examined regarding their relationship to the intervention by the independent DSMB. In case such a relationship is assumed or cannot be ruled out completely, the following rules apply. Occurrence of any serious or fatal adverse events will lead to the discontinuation of the trial. Occurrence of severe serious and moderate serious adverse events will lead to substantial revisions of the study design, for example, by limiting total treatment duration or reducing the dosage of rnTMS. Actions for not serious severe and moderate adverse events depend on the number of subjects presenting with an adverse event as well as the reversibility of the adverse event. Actions might include similar changes in study design, reductions in dosage, or temporary recruitment stops until further analysis of adverse events. Mild adverse events in any number of subjects as well as moderate not serious (≤ 3 patients if reversible; ≤ 1 patient if not reversible) and severe not serious (≤ 1 patient if reversible) adverse events require no action.

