### Criteria for discontinuing or modifying allocated interventions {11b}

Patients can withdraw from the trial on their own wish at any point without any disadvantages. They will also be released from the trial in case of immediate need for surgery, for example, due to a progressing tumor, or conflicting recommended or necessary medical treatments. Occurrence of serious moderate, serious or severe, life-threatening, or fatal adverse events will lead to exclusion of the participant. In case of moderate, but not serious adverse events treatment may be continued, modified, or discontinued based on the judgment of the independent Data and Safety Monitoring Board (DSMB).

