### Composition of the data monitoring committee, its role and reporting structure {21a}

An independent external Data and Safety Monitoring Board will monitor the trial. The board will consist of two consultant neurosurgeons with experience in nTMS, an expert on biomedical engineering and development of new nTMS technology, and an independent biostatistician. The independent experts will conduct semi-annual meetings starting with recruitment onset to discuss any issues arising from monitoring reports; specifically, the DSMB will evaluate the accumulated trial data for patient safety, study conduct, and progress, and will make recommendations concerning continuation, modification, or termination of the trial.

In case of any unforeseen deaths or occurrence of a serious adverse event (SAE), the board will conduct an ad hoc review of the severity and relatedness of the events to the intervention. Finally, the board will participate in annual meetings organized by the study group. Minutes of these meetings will document any feedback given by the expert committee and be provided to the BMBF/DLR in the interest of full disclosure.

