### Adverse event reporting and harms {22}

All (serious) adverse events ((S)AEs) will be collected from the date the informed consent form is signed until the final study visit. For events that occur between postoperative follow-ups, participants are queried on a routine basis about every 2 weeks starting from postoperative day 7. (S)AEs will be captured on case report forms according to MedDRA, including event description; time of onset; assessment of seriousness, severity, relationship to study procedures or interventions, and expectedness; medical care received; outcome of event; and time of resolution/stabilization of the event. All (S)AEs occurring during the trial are documented appropriately regardless of their relationship to the intervention. All (S)AEs will be followed until satisfactory resolution or the participant is stable. All (S)AEs will be assessed by the investigator for severity, expectedness, and relationship to the intervention using the protocol-specified definitions.

Documentation of AEs will be reported to Clinical Trial Management within 7 days. All AEs are reported in aggregate as part of the routine data and safety monitoring report provided to the DSMB and the BMBF/DLR by the Clinical Trial Management. AEs are reported to the IRB as part of the continuing review. SAEs (regardless of expectedness or relatedness) will be reported to the DSMB and BMBF/DLR within 48 h of the investigator becoming aware of the event. Previous trials of the same duration and similar doses did not show any SAEs related to the intervention.

Based on our previous trial on postoperative rnTMS therapy (SAE = 0, AE = 0 in 16 patients with each 7 rnTMS sessions; see in [12]) and pilot study on accelerated rnTMS in healthy subjects (SAE = 0, AE = 5 in 3 subjects with each 14 rnTMS sessions; see in [10]), we expect AEs: *n* = 30 (mild headache); *n* = 50 (tiredness due to intensive stimulation and training); *n* = 10 (dizziness); SAEs: *n* = 0.

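### The safety rules require both stopping and redesigning the trial after a possibly related severe or moderate serious adverse event

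*Protocol article*

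**What the plan says.** The rules stand in one paragraph of the protocol article, under Interim analyses {21b}. No interim efficacy analysis is planned. The DSMB examines each event's relationship to the intervention, and one condition opens all the rules: "In case such a relationship is assumed or cannot be ruled out completely, the following rules apply".

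Three of the rules matter here:

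- Stop: "Occurrence of any serious or fatal adverse events will lead to the discontinuation of the trial".
- Redesign: "Occurrence of severe serious and moderate serious adverse events will lead to substantial revisions of the study design", with the illustration "for example, by limiting total treatment duration or reducing the dosage of rnTMS".
- No action: "Mild adverse events in any number of subjects", listed together with small numbers of moderate and severe events that are expressly non-serious.

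Three other sections bear on how these are read. Adverse event reporting and harms {22} has each event documented with "assessment of seriousness, severity, relationship to study procedures or interventions, and expectedness". Criteria for discontinuing or modifying allocated interventions {11b} has a participant-level rule with its own ladder: "Occurrence of serious moderate, serious or severe, life-threatening, or fatal adverse events will lead to exclusion of the participant". The section on the data monitoring committee {21a} has the DSMB review every serious adverse event ad hoc and says that it "will make recommendations concerning continuation, modification, or termination of the trial".

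**The concern.** A stopping rule for safety should give one answer for each kind of event it names. Here the first two rules share a trigger and are both phrased as certain consequences, yet one ends the trial and the other changes the dose or duration of a trial that goes on. If both apply to the same event, the text cannot be followed.

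The question at stake is whether a single possibly related serious event ends a 148-patient trial or modifies it. The DSMB, the sponsor and the ethics committee should know the answer before such an event occurs. Otherwise it will be argued afterwards, case by case.

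**Working it through.** The article gives no figure to reproduce and no arithmetic applies, so the check sets the rules side by side.

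**Step 1: same trigger.** The sentence on the causal relationship precedes all the rules, so they cannot be separated by degree of relatedness.

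**Step 2: does one class contain the other?** Section {22} records seriousness and severity as two attributes. A severe serious event is then a serious event that is also graded severe, and likewise for moderate. The stop rule says *any* serious event and gives no severity limit. Both classes named in the redesign rule fall inside it.

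**Step 3: can both actions be carried out?** Shortening treatment or lowering the dose presupposes further participants to treat. A discontinued trial has none. The actions are incompatible.

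**Step 4: is there a precedence rule?** None in {21b}. Section {11b} governs the individual participant. Section {21a} gives the DSMB a general power to recommend and does not rank the rules.

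**Step 5: cross-table for possibly related events, as written.**

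| Event | Stop rule | Redesign rule | No-action rule | Result |
|---|---|---|---|---|
| Fatal | stop | – | – | one action |
| Severe serious | stop | redesign | – | incompatible |
| Moderate serious | stop | redesign | – | incompatible |
| Mild serious (class never named) | stop | – | only if *mild* is read without limit | conflict on that reading only |
| Severe or moderate, not serious | – | – | depends on count and reversibility | no overlap with the stop rule |
| Mild, not serious | – | – | no action | one action |

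Life-threatening events do not appear in {21b}. If they are taken as serious, which is an assumption, they fall under the stop rule alone.

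**Step 6: test the repairs.**

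- *Change only the stop rule, to life-threatening or fatal.* Severe and moderate serious events map to redesign alone. Read literally, though, a possibly related mild serious event would then have no action as its only rule. The no-action rule must therefore also be limited to non-serious events.
- *Make both changes, and send mild serious events to the DSMB's ad hoc review.* Every row has one route.
- *Keep the stop rule and delete only the redesign rule for serious events.* The mild serious row still meets two rules on the literal reading. Limiting the mild rule to non-serious events clears it.

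**The case against.** **A workable reading exists.** The paragraph can be taken as a descending ladder in which the specific sentence on severe and moderate serious events carves them out of the general one. The ladder in {11b}, which ends in life-threatening and fatal, suggests that *serious* in the stop rule is a slip for *life-threatening*. This is plausible and softens the defect. It remains inference: {21b} never uses the term life-threatening, the word *any* cuts against a carve-out, and a stricter reader could as fairly stop the trial.

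**The DSMB decides in any case.** Every serious event is reviewed ad hoc and the board may recommend continuation, modification or termination. That stands, so a reader who inferred that serious events could go unreviewed would be wrong. But {21b} fixes consequences in advance, and those are what conflict. A DSMB charter, which is not shown, might settle precedence; the protocol text does not.

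**An article condenses.** Brevity explains what is left out. It does not explain two printed statements that cannot both be followed.

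**No serious events are expected.** Section {22} does expect none, citing none in 16 patients with 7 sessions each. Zero in 16 is compatible with a true rate of up to 1 − 0.05^(1/16) ≈ 17% (one-sided 95% bound). Participants here may receive up to 2 × 28 = 56 sessions, and the rules apply whenever a link cannot be ruled out. The rule may well be needed.

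**The mild serious case is weak.** This objection largely stands. A reader might infer that every non-fatal serious grade is in conflict, or count conflicting cells on a five-step severity scale. The documents do not support that. No section names a mild serious event, the mild clause sits in a sentence otherwise about non-serious events, and a five-step scale would have to be assembled from two sections. Only an unqualified word is left to tidy up.

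**Conclusion.** The stated safety rule contradicts itself for two named classes: possibly related severe serious and moderate serious events. Each carries two mandatory, incompatible actions with no order of precedence. The conclusion rests on reading *any serious* at face value and on section {22} treating seriousness and severity as separate attributes. The unlimited scope of the mild no-action rule is a secondary drafting point.

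Alpha, power, sample size and effect estimates are untouched. Events judged unrelated trigger none of these rules. The point does not show that oversight is absent or that the trial is invalid. It is a real defect in a decision rule, cheap to repair, and it should be fixed before a qualifying event occurs.

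**What to change.** Amend {21b} in three places:

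1. Stop the trial for possibly related life-threatening or fatal events, using the grades that {11b} already names.
2. Keep redesign for severe and moderate serious events.
3. Limit the no-action rule to mild events that are not serious, and send any mild serious event to the ad hoc DSMB review already required by {21a}.

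The cost is a short protocol amendment, with DSMB charter wording matched if needed. The substantive downside is that a related severe or moderate serious event would no longer stop the trial automatically, although the DSMB could still recommend termination. Because this adopts the less conservative reading, the sponsor should confirm that it is the intended one.

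If the sponsor does mean to stop for any related serious event, it should delete the redesign rule for serious events and limit the mild rule to non-serious events. Under that version a single possibly related serious event of any severity would end the trial.

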## Introduction

### Background and rationale {6a}

Around 8300 cancers of the central nervous system and 6140 deaths are reported in Germany every year [1]. These cancers are associated with 150,993 disability-adjusted life years reported in 2016 [1]. Furthermore, an increase in sick leave is observed in these patients before surgery with a return-to-work rate of only 50% 1 year after surgery [2], thus presenting a major socioeconomic burden. While maximal surgical resection has been linked with improved overall survival, up to 50% of intrinsic brain tumors are not completely resected due to infiltration of functional brain tissue. In addition, up to 25% of patients with brain tumors in motor areas suffer from new or worsened motor deficits postoperatively. Both, incomplete tumor resection and impaired neurological status, are directly correlated with decreased life expectancy [3, 4]. While surgical resection is the most effective treatment option for intrinsic brain tumors, traditionally, tumors that have been demonstrated to infiltrate functional tissue will be diagnosed as inoperable and will be treated conservatively from then on. However, in recent years the concept of neurological functions being confined to specific areas of the brain has been questioned and a novel concept of function being represented in dynamic cortico-subcortical networks has been introduced [5]. This paradigm shift also implies that function can move, for example, due to the presence of a pathology — yet typically, the reshaping is too slow or ineffective to sustainably affect the clinical course of the patient.

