### Procedure for unblinding if needed {17b}

Premature unblinding of a study patient can be considered for medical reasons and in case of severe adverse events. Attending physicians and investigators are encouraged to discuss these requests with the principal investigator. The reason, time, and date of the unblinding will be documented on case report forms (CRF) and study monitors will be informed.

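### The safety rules in {21b} assign the same serious event to both stopping the trial and continuing it with a revised design

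*Protocol article*

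**What the plan says.** Section {21b} plans no interim analysis and has the independent DSMB examine each event's relationship to the intervention. A condition then opens the rules: "In case such a relationship is assumed or cannot be ruled out completely, the following rules apply". Four tiers follow:

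- Top tier: "Occurrence of any serious or fatal adverse events will lead to the discontinuation of the trial".
- Second tier: "Occurrence of severe serious and moderate serious adverse events will lead to substantial revisions of the study design". The examples given are a shorter total treatment duration and a lower rnTMS dose, so the trial goes on.
- Third tier: severe or moderate events that are not serious. The action depends on the number of patients affected and on reversibility.
- Last tier: mild events, and small numbers of non-serious moderate or severe events, need no action.

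Two other sections bear on the point. Section {11b} has a rule for the individual participant: "Occurrence of serious moderate, serious or severe, life-threatening, or fatal adverse events will lead to exclusion of the participant". Section {21a} says that after an unforeseen death or a serious adverse event "the board will conduct an ad hoc review of the severity and relatedness of the events to the intervention". It also gives the board the task of recommending whether the trial should continue, change or end.

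**The concern.** The two top tiers overlap. The first covers every serious event, and the second covers a subset of serious events and prescribes a different action. For that subset the protocol requires both ending the trial and carrying on with a modified intervention, and these cannot both be done.

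This would matter at the first moderate or severe serious event that the board cannot fully separate from the stimulation. On one reading recruitment ends before the planned 148 patients, and the two primary hypotheses are not tested at their intended size. On the other, recruitment goes on with a changed duration or dose. A choice of that weight should be fixed before the event. If it is made afterwards, the people choosing already know which event prompted it.

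**Working it through.** No arithmetic applies, because the rules carry no error rate, count or computed figure for serious events. The check is whether the tiers can be followed together.

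**Step 1: is a moderate or severe serious event a serious event?** Yes. Section {22} records seriousness and severity as separate attributes of each event. Section {21b} uses them the same way, combining a severity grade with serious or not serious. The class of any serious event therefore contains the moderate serious and the severe serious ones.

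**Step 2: put the actions side by side, for events that pass the relatedness condition.**

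| Event | First rule, as written | Second rule, as written |
|---|---|---|
| Fatal | discontinue | not mentioned |
| Life-threatening, serious | discontinue | not mentioned |
| Severe, serious | discontinue | revise and continue |
| Moderate, serious | discontinue | revise and continue |

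The last two rows conflict. They are also the only rows that the second rule covers. If the first rule prevails, the second has no case left to act on.

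**Step 3: does another section decide between them?**

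- {11b} names moderate, severe, life-threatening and fatal events. Set against {21b}, this suggests a ladder in which the top two grades stop the trial and the middle two lead to revision. But {11b} concerns exclusion of a participant, and it assigns all these grades the same action. It hints at the intent for {21b} without stating it.
- {21a} makes the board advisory, with three possible recommendations. It does not say which one goes with which grade. It also sits uneasily with {21b}, where both rules are worded as mandatory.
- {22} describes collection and reporting of events and sets no trial-level action.

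No section shown resolves the overlap.

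**The case against.** The strongest reply is that this is a slip of wording whose intent is clear. The tiers in {21b} run in descending order, the second sentence has a purpose only if the first is confined to the higher grades, and {11b} names those grades. A specific rule would normally be read as overriding a general one. In addition, an independent board that includes a biostatistician reviews each serious event and recommends what to do, so there need be no deadlock. A board charter or the full protocol may also be clearer.

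Much of this stands. The narrower reading is probably what was meant, and a sensible board could find its way. But the board would be choosing between two mandatory sentences, and the first says any serious event. A document that is not shown might clarify the rule, yet the published text states it and states it inconsistently.

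A reader might infer something stronger: that one background event, such as a postoperative motor deficit or a habitual seizure, could end the trial without any comparison with sham, and that such events should be exempted. Events are collected through surgery and follow-up (they "will be collected from the date the informed consent form is signed until the final study visit"), and the background section reports that "up to 25% of patients with brain tumors in motor areas suffer from new or worsened motor deficits postoperatively". The documents do not support this step:

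- They do not class such deficits or seizures as serious. They also do not show the relatedness definitions that the board would use, so nothing says such events would pass the condition.
- They give no rate of serious events that cannot be excluded as related. They do not say whether the board sees allocation; {17b} says only that "Premature unblinding of a study patient can be considered for medical reasons and in case of severe adverse events". Any probability of a trigger would be assumed throughout.
- A single-case trigger is a defensible choice in an exploratory phase 2b trial whose earlier safety data in patients come from 16 people. Comparison with sham would be slow to detect harm: with 74 per arm, a one-sided Fisher test gives p = 0.060 for 4 events against 0, and p = 0.029 for 5 against 0.

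**Conclusion.** The rule is wrong as written. For every moderate or severe serious event whose link to the intervention is assumed or cannot be fully excluded, {21b} prescribes two incompatible actions, and taken literally its revision tier is empty. This follows from the wording alone and rests on no assumed rate.

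The practical size cannot be put as a probability. Section {22} expects no serious adverse events, so the conflict may never arise. If it does, the outcome turns on which sentence is followed: the trial ends, or it continues with a changed intervention. The point does not extend to the sensitivity of the trigger. Acting on a single related serious event is the sponsor's choice to make, provided the text says which action follows.

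**What to change.** Reword the first rule in {21b} so that life-threatening or fatal serious adverse events lead to discontinuation, and keep the second rule for moderate and severe serious events. The tiers then no longer overlap, and they match the grades named in {11b}.

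If the sponsor does intend to stop for any related serious event, keep the first rule and delete the revision tier. In that case the closing no-action rule for mild events should also be limited to non-serious ones, so that it does not create a similar overlap.

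Either way, add a clause saying whether the {21b} actions bind the trial or guide the board's recommendation under {21a}.

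The cost is one or two sentences in a protocol amendment and the same wording in the board's charter. Sample size, endpoints and analysis are unaffected. The first option does give up an automatic stop at the first moderate or severe serious event, so the sponsor should choose it deliberately and settle it before such an event occurs.
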